**Effectiveness outcomes**				
Primary outcomes:				
Time from referral to first appointment	✓			
Proportion of patients seen within thresholds	✓			
Number of patients on the waiting list	✓			
Covariates:				
Demographic data	✓			
Referral data	✓			
Secondary outcomes:				
Health service use (outpatient services, emergency presentations and health service admissions)	✓			
**Implementation outcomes**				
**Adoption**				
Evidence of targeted backlog reduction activity				
Strategies implemented			✓	
Evidence of protected capacity for new patients				
Number of weekly appointments scheduled for new and review patients	✓			
Evidence of changes to model of care				
Staff perceptions of service changes			✓	
Patient experience of services		✓		
**Fidelity**				
Descriptive analysis of backlog reduction activity				
Number of patients removed from list				✓
Reasons for removal (appointment previously provided, service not needed, unable to contact)				✓
Number of patients scheduled for care				✓
Ratio of expected demand to new patient appointments booked	✓			
Indicators of change in care delivery				
Mode of delivery (face to face, telehealth)	✓			
Number of appointments scheduled by professional type (medical, nurse, allied health)				
Appointment outcomes (proportion rebooked/discharged)	✓			
Attendance (expressed as proportion failed to attend)	✓			
Ratio of new to review patients scheduled	✓			
Contacts with clinic staff outside of the allocated clinic appointments (eg, telephone advice and follow-up)				✓
**Acceptability, feasibility and appropriateness**				
Patient perceptions		✓		
Staff perceptions			✓	
**Cost**				
Costs to health service:				
Backlog reduction strategies				✓
Service delivery	✓			
Revenue	✓			

### Sample size

A minimum average of 400 referrals is expected to be received for each included specialty annually (100 per quarter), resulting in at least 700 patients across the pre- and post-implementation periods for each cluster (minimum total sample, n=5600). With four steps and eight clusters (two clusters per step), this stepped wedge design will be well powered to detect even small-to-moderate effect sizes. For a mean difference of 0.25 SD in waiting time and a conservative ICC of 0.1, with at least 60 referrals per cluster per 3-month time period (which is less than the pro-rata expected number annually), this design is powered at approximately 90% to sufficiently detect a difference at a 5% level of significance.^38
39^ Again, under conservative assumptions, power for detecting significant differences for our secondary outcomes (eg, an increase in the proportion of urgent patients seen within 30 days from 80 to 90%) exceeds 90%. Compared with our findings from STAT implementation in community outpatient services,^27^ our power and sample size assumptions are chosen conservatively to more than compensate for additional heterogeneity or other differences in the specialised clinic setting.

The sample size for quantitative implementation outcomes is based on the duration of the intervention and length of the waiting lists of the included services. The sample size for the qualitative analysis is considered feasible and expected to be sufficient to reach information power.

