### Outcome measures

#### Effectiveness outcomes

Quantitative outcomes will be obtained from routinely collected healthcare data and auditing of health service processes. The primary outcome measure for effectiveness will be waiting, measured as time from initial referral to first appointment and the number of people on the waiting list (measured weekly). Secondary outcomes include the number of emergency department presentations and days admitted to the health service during the 6 months prior to and following the first clinic assessment to determine whether there is a relationship between improved specialist clinic access and other health service utilisation (outpatient services, emergency presentations and health service admissions). These data will be collected for a subgroup of patients attending the clinic for the first time within two of the pre- and post-implementation time blocks (darker shades in figure 1). Factors that may be covariates that impact on waiting times will also be recorded (demographic data, diagnosis and referral source).

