Acceptability, feasibility and appropriateness will be evaluated using qualitative data from staff and patients. Staff perspectives will be sought during the pre-implementation and implementation periods (perceptions of current state, views about the intervention and challenges/enablers for implementation) as well as 6 months after the commencement of the post-implementation period (perceived success or failure of the intervention, impact on patient care, staff workloads and job satisfaction and reflections on feasibility and appropriateness of the STAT model for specialist clinics). Patient perspectives of the clinic service will be sought from samples of patients who attend during the pre- and post-implementation periods.

The total cost of implementation will be considered in two parts: (i) Cost of initial backlog reduction (auditing and short-term additional supply) per patient removed from the waiting list and (ii) total cost of clinic operations during the pre- and post-implementation periods. The cost-effectiveness of the STAT programme will determine the incremental cost per percentage of urgent referrals seen within 30 days and routine referrals seen within 90 days, comparing usual care conditions to intervention conditions. Individual patient health service utilisation cost (outpatient services, emergency presentations and health service admissions) will be collected for the 6 months prior to their first clinic appointment and the first 6 months following this appointment, for patients under usual care conditions and for patients under intervention conditions (estimated n=800).

Outcome measures across all aspects of the trial are summarised in table 3.

**Table 3 T3:** Summary of outcome measures and data sources

	Routinely collected data	Consumer interviews	Staff focus groups	Prospective audits

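### The power above 90% claimed for the secondary outcomes is not supported for health service use, the outcome the protocol names as secondary and collects only in a subgroup

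*Protocol article*

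**What the plan says.** All references are to the protocol article.

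- **Sample size, primary outcome.** The effect and correlation assumed are "For a mean difference of 0.25 SD in waiting time and a conservative ICC of 0.1". The cell size is stated separately as "with at least 60 referrals per cluster per 3-month time period", and the design is described as "powered at approximately 90% to sufficiently detect a difference at a 5% level of significance". The minimum total is 5600.
- **Sample size, secondary outcomes.** The next sentence extends the claim to "power for detecting significant differences for our secondary outcomes". The one example is "an increase in the proportion of urgent patients seen within 30 days from 80 to 90%) exceeds 90" per cent.
- **Effectiveness outcomes.** The secondary outcomes named are emergency presentations and days admitted in the 6 months before and after the first clinic assessment. On their collection: "These data will be collected for a subgroup of patients attending the clinic for the first time". The visits that count are those in two of the pre- and post-implementation blocks, which are shaded in Figure 1.
- **Implementation outcomes.** The cost of the same kinds of service use, over the same 6-month windows, is to be collected "for patients under usual care conditions and for patients under intervention conditions (estimated n=800").
- **Table 3.** The proportion seen within thresholds stands under primary outcomes. The only secondary entry is "Health service use (outpatient services, emergency presentations and health service admissions"), marked as routinely collected data.
- **Analysis, Effectiveness.** Secondary outcomes get generalised linear mixed models, binomial for proportions and negative binomial for counts.

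**The concern.** The power sentence covers the secondary outcomes as a class, but nothing in it relates to the outcomes that the protocol elsewhere names as secondary. The example belongs to another outcome, which Table 3 calls primary. The cluster-period size behind the paragraph appears to be well above what the utilisation data will have. A power figure for a count outcome also needs an effect size, an event rate and a dispersion, and none is stated.

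This matters because the strengths and limitations box offers health service use as the proxy for changes in health status, to offset the lack of direct patient outcomes. A reader who trusts the stated power would take a null finding on emergency visits or bed days as evidence that faster access made no difference. At the precision likely to be available, such a finding would say little either way.

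**Working it through.** **Layout.** The Design section gives 6 months of control data, then two clusters every 3 months over four steps, each with a 6-month implementation period. The study lasts 27 months, or 9 quarters. Clusters at step s (1 to 4) therefore have pre data in quarters 1 to s+1, no data in quarters s+2 and s+3, and post data from quarter s+4 to 9. That is 7 observed quarters per cluster, and 8 × 7 × 100 = 5600 reproduces the stated minimum.

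**Subgroup size (derived, not printed).** Reading the text as two pre and two post blocks per cluster, and taking the 800 as this subgroup: 800/(8 × 4) = 25 per cluster-quarter, and 800/5600 = 1/7.

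**Model.** Cluster random intercept, quarter as a factor, constant effect, total variance 1, ICC ρ, m patients per cell, two-sided 5%:
- V_i = ρJ + ((1−ρ)/m)I
- Var(θ̂) = the treatment diagonal of (Σ X_i′V_i⁻¹X_i)⁻¹
- power = Φ(δ/SE − 1.96)
- effect detectable with 90% power = (1.96 + 1.28) × SE

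**The plan's own figures first.** Five quarters, no gap, m = 60, ρ = 0.1 gives SE = 0.0700.
- Primary: 0.25/0.0700 − 1.96 = 1.61, power 94.6% against the stated approximately 90%.
- Example: mean variance (0.8 × 0.2 + 0.9 × 0.1)/2 = 0.125, SD 0.354, so 0.10 is 0.283 SD. Then 0.283/0.0700 − 1.96 = 2.08, power 98%.

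The claim above 90% therefore reproduces for the example, if all 60 are urgent patients (at least 39 are needed) and there is no gap. With the 2-quarter gap, the same inputs give 56% for the example and 46% for the primary.

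**Health service use.** No effect size is printed, so the plan's 0.25 SD is borrowed. ICC runs from 0.01 to 0.1.

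| Layout | m | Patients | Power for 0.25 SD | Effect detectable at 90% |
|---|---|---|---|---|
| Printed timeline, last two pre and first two post quarters | 25 | 800 | 16-21% | 0.71-0.86 SD |
| Same blocks | 100 | 3200 | 41-52% | 0.41-0.47 SD |
| Printed timeline, all pre and post quarters | 100 | 5600 | 64-68% | 0.34-0.35 SD |
| Five-period wedge, no gap | 20 | 800 | 55-61% | 0.36-0.39 SD |

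Worked line for row 1 at ρ = 0.1: SE = 0.264; 0.25/0.264 − 1.96 = −1.01; power 16%; detectable effect 3.24 × 0.264 = 0.86 SD.

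**Sensitivity.**
- Most favourable choice of two pre and two post blocks on the printed timeline: 21% at ρ = 0.1.
- 800 per condition (1600 patients, m = 50), ρ = 0.1: 25-36% with the gap, 69% without.
- One pre and one post block (m = 50, 800 patients), adjacent: 11% with the gap.
- Negative binomial on the log scale, variance 1/μ + k. Assumed: mean 0.3 to 1.0, k = 1, rate ratio 0.66. Power is 10-26% on the printed timeline and 25-79% in no-gap layouts at m = 25. It is lower at a rate ratio of 0.80.
- No calendar-time adjustment, ρ = 0.1: SE² = 2 × 0.9/(8 × 50) = 0.0045, SE = 0.067, power 96%.

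**Why the gap matters.** On the printed timeline, step 1 post data start in quarter 5 and step 4 pre data end in quarter 5. That is the only quarter in which both conditions are observed.

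**The case against.** The strongest reply is that the subgroup is not what breaks the claim. With all 5600 first attenders, power for 0.25 SD is still only 64-68%, because the 6-month implementation gap removes most of the concurrent comparison. That stands. A reader might infer that the restriction to 800 is the sole cause, and the numbers do not support this. The subgroup is enough to defeat the claim even without a gap (55-61%), but on the printed timeline both act.

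Second, the inputs are partly inferred. The subgroup has no printed size in the Effectiveness outcomes section. The 800 comes from the costing text and is linked only by matching data and windows. Block positions are in a figure not shown, and 0.25 SD was stated for waiting time. These points stand. They make 16-21% an illustration under stated assumptions, not the trial's actual power for emergency visits. A reader might go further and infer that the effect cannot be estimated at all because the blocks never overlap in calendar time. That would follow only from particular block positions, which the text does not state.

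Third, the Analysis section ties the time-point factor expressly to the primary outcome. Without calendar adjustment, power at 800 is 96%. That is a plain before-after comparison, however, and gives up the stepped wedge's control for time. The calculation also takes no credit for precision gained from the prior 6 months' use.

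Fourth, the claim reproduces for its own example, which the Sample size section calls secondary. This shows that the sentence was probably computed for that outcome. It does not extend the figure to health service use, and it leaves the conflict with Table 3.

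**Conclusion.** The concern holds as a correction to a stated figure. Power above 90% for the secondary outcomes is not supported for the outcomes the protocol names as secondary. The mismatch in labels and sample base can be read directly from the text. The size depends on three assumptions: the subgroup is about 800, calendar time is in the model, and 0.25 SD is a fair yardstick. Power is then about 16-21% on the printed timeline with adjacent blocks, and 55-61% in a five-period wedge with no gap. At 800 patients, over 90% appeared only when calendar time was left out.

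Exact power for emergency visits or admitted days cannot be computed, because no effect size, rate or dispersion is given. A null result is therefore not shown to be near-certain. The supportable statement is that a null result would be uninformative. The defect is in the power statement. Collecting a secondary outcome in a subgroup is a legitimate choice if its precision is described honestly.

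**What to change.** 1. **Sample size.** Limit the power statement to the threshold proportion it was computed for. State the number of urgent patients per cluster-quarter and the period layout assumed, since the figure reproduces only without the implementation gap.
2. **Label.** Make that outcome primary or secondary consistently across Sample size, Effectiveness outcomes, Analysis and Table 3.
3. **Health service use.** State its subgroup size where the outcome is defined. Say that it is not powered at 90%, will be reported by estimate and confidence interval, and that a null result will not be read as evidence of no effect.

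These are wording changes. Their cost is a less favourable stated power.

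4. **Optional.** Table 3 marks health service use as routinely collected, so it could be extracted for all first attenders whose 6-month follow-up window is complete. Power for 0.25 SD would rise to at most about 64-68% with all 5600, still short of 90%, so items 1 to 3 are needed regardless. The cost is more data-management time and possibly a later extract. Patients first seen in the last two quarters do not have 6 months of follow-up by 27 June 2027, and on the printed timeline those are the only post quarters of the step 4 clusters. The 64-68% assumes that their follow-up is obtained.

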## Method

### Setting

The trial will take place at Eastern Health, a large network of metropolitan services in the eastern suburbs of Melbourne, Australia, providing publicly funded health services to a diverse community of approximately 892 000 people, including a high proportion (32%) of residents born overseas. Eastern Health offers a broad range of services, including emergency care, surgery, maternity, palliative care, mental health, drug and alcohol services, residential care and community health, delivered across three tertiary hospitals, two sub-acute inpatient services, a small community hospital, a day surgery centre and more than 30 community sites. The inclusion of a single health service could be seen as a limitation, but the size of the health network and its operation across multiple sites spanning a diverse geographical catchment provide confidence in the applicability of the findings to a broad range of health settings.

Eastern Health operates a comprehensive network of specialist medical clinics, providing expert care across a broad range of medical disciplines. Patients are typically referred to these clinics by general practitioners, specialists or hospital-based clinicians. Referrals are made electronically, then triaged by clinicians and assigned a priority category. Urgent referrals may be booked directly into appointments, while routine referrals are waitlisted until an appointment becomes available. Waiting times vary from weeks or months to several years.

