#### Effectiveness

Linear mixed effects models will be used to analyse data related to the primary outcome with time-point (time since trial start) and time since intervention as factor variables. This allows for the expected nonlinear change over time, as well as an analysis of persistence of intervention and time-averaged intervention effects following the service redesign, consistent with recommendations.^40^ Generalised linear mixed effects models will be used to analyse the secondary outcomes (binomial for proportions and negative binomial for counts to allow for over-dispersion). A random effect for the clinic will be used for all models to account for clustering. Visual diagnostics will be used to assess model assumption validity, and transformations of outcomes or robust estimators will be used as needed. Adjusting for and analysing the association between covariates (eg, referral source and demographic data, including potential indicators of disadvantage such as need for interpreters) and outcomes will also be completed by including these in the mixed-effects models as predictors. Given the small number of clusters, the Kenward-Roger small-sample correction will be used for the df for inference of the fixed effects.^41^

In the event of any system-wide (eg, pandemic) and within-cluster notable disruptions (eg, staffing issues) that are not adequately captured by the baseline random-effects structure and residual variation, a disruption indicator variable will be used for the disrupted time period. This model of adjustment to disruption can also be included as an indicator within affected clusters only. As an additional sensitivity analysis, within-cluster time-series analyses will be conducted to account for localised temporal disruptions while assessing the persistence of intervention effects. R V.4.4.1 (or a newer version if available) will be used for the analyses.

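### The power above 90% for urgent patients seen within 30 days does not follow from the stated inputs, and the pre/post layout described does not reach it at any urgent share of the stated referrals

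*Protocol article*

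**What the plan says.** The Sample size section starts from total referrals: "A minimum average of 400 referrals is expected to be received for each included specialty annually (100 per quarter"). From this it derives a patient total for every specialty, "resulting in at least 700 patients across the pre- and post-implementation periods for each cluster". The waiting-time calculation opens with its effect size and correlation, "For a mean difference of 0.25 SD in waiting time and a conservative ICC of 0.1". It then fixes the cell size, "with at least 60 referrals per cluster per 3-month time period", and reports power of approximately 90% at the 5% level.

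The next sentence turns to secondary outcomes. On assumptions it calls conservative, power for "an increase in the proportion of urgent patients seen within 30 days from 80 to 90%) exceeds 90" per cent. It gives no cell size, urgent count or ICC for this outcome.

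The Setting section shows that urgent referrals are only part of the total: "Urgent referrals may be booked directly into appointments, while routine referrals are waitlisted until an appointment becomes available". The economic sections give routine referrals their own 90-day threshold. The Effectiveness analysis section plans generalised linear mixed models for secondary outcomes ("binomial for proportions and negative binomial for counts to allow for over-dispersion"), with a random effect for clinic.

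On timing, the Design section gives six months of control data, two clusters starting every three months, and six months of implementation in each cluster before post-implementation data begin. The routine-data section draws effectiveness outcomes from the pre- and post-implementation periods. The health economics section puts the study at 27 months.

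**The concern.** Two things stand between the stated inputs and the printed power. The denominator is urgent patients, whereas the stated cell sizes cover every referral. In addition, each cluster's two implementation quarters supply no effectiveness data. In a stepped wedge those quarters, on either side of the switch, carry much of the information about the effect.

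The stake is interpretation. Urgent referrals seen within 30 days form one part of the effect measure in the cost-effectiveness ratio, and one part of the broader measure of patients seen within thresholds that Table 3 lists under primary outcomes. A reader told that power exceeds 90% would take a null result as good evidence that urgent access did not improve.

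**Working it through.** **Inputs from the article.** 8 clusters, 4 steps, 2 clusters per step; proportions 0.80 and 0.90; 5% level, taken as two-sided; 60 referrals (100 expected) per cluster-quarter; 27 months = 9 quarters; 2 control quarters before the first step; 2 implementation quarters per cluster.

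**Assumptions.** The ICC of 0.1 is stated for waiting time and carried over. The urgent share is not given, so 20, 30 and 50% of 60 are used: 12, 18 and 30 urgent patients per cluster-quarter. The effect is constant after the switch.

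**Layout check.** 9 − 2 = 7 analysed quarters per cluster; 7 × 100 = 700 and 8 × 700 = 5600. These are the plan's own totals, so its patient count already leaves out the implementation quarters. They split into 28 control and 28 intervention cluster-quarters.

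**Method.** Generalised least squares on cluster-quarter means, with quarter as a factor and a random cluster intercept. With v = 0.85 × 0.15 = 0.1275 and m urgent patients per cell, the within-cell variance is s² = 0.9v/m and the cluster variance is τ² = 0.1v = 0.01275. Power = Φ(0.10/SE − 1.96). For a complete wedge with I clusters and T quarters,

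Var = I·s²(s² + Tτ²) / [(IU − W)s² + (U² + ITU − TW − IV)τ²],

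where U is the number of treated cells, W the sum over quarters of squared treated counts, and V the same sum over clusters.

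**The plan's waiting-time figure first.** Five-quarter wedge: U = 20, W = 120, V = 60, so the brackets are 160 − 120 = 40 and 400 + 800 − 600 − 480 = 120. For 0.25 SD and m = 60: s² = 0.015, τ² = 0.1, Var = 8 × 0.015 × 0.515 / (0.6 + 12) = 0.00490, SE = 0.070, and power = Φ(3.57 − 1.96) = 95%. Nine quarters without a gap give 98%. With the gap, the result is 47%. The stated 90% is therefore approached only when the gap is ignored.

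**Urgent outcome, worked case.** Five-quarter wedge, m = 18: s² = 0.006375, Var = 8 × 0.006375 × 0.070125 / (0.255 + 1.53) = 0.00200, SE = 0.0448, power = Φ(2.23 − 1.96) = 61%.

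**Plan's layout.** The same least-squares calculation with the implementation cells removed gives SE = 0.0477 at m = 60, so power = Φ(2.10 − 1.96) = 55%. At m = 100, SE = 0.0370 and power = 77%.

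| Urgent per cluster-quarter | Five-quarter wedge, no gap | Nine quarters, no gap | Pre/post quarters only |
|---|---|---|---|
| 12 (20% of 60) | 46% | 53% | 16% |
| 18 (30% of 60) | 61% | 70% | 21% |
| 30 (50% of 60) | 81% | 89% | 32% |
| 40 | 91% | 96% | 40% |
| 60 (all of 60) | 98% | 99.5% | 55% |
| 100 (all expected) | 99.9% | over 99.9% | 77% |

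Power of 90% needs about 40 urgent patients per cell in the five-quarter wedge, about 31 with nine quarters and no gap, and about 144 in the plan's layout, which exceeds the 100 expected referrals of all kinds.

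**Sensitivity in the plan's layout.** The smallest variance, 0.9 × 0.1 = 0.09, gives 70% at m = 60 and 89.6% at m = 100. With v = 0.1275 and the ICC varied from 0.001 to 0.2, power at m = 100 is at most 82%. A time-averaged effect, allowing for time since intervention, lowers power at m = 60 to 33%. A logistic mixed-model information calculation agrees within about 5 points.

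**The case against.** The best defence is that the article ties 60 per cell to waiting time only and gives no cell size for the urgent outcome. If 31 to 40 of the 100 expected referrals are urgent, a wedge without a gap does exceed 90%, and the article is a condensed account. This stands in part: on the denominator alone, the figure is unsupported rather than shown to be false.

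A reader might also infer a contradiction with the waiting-time power, because 0.10/√0.16 = 0.25 SD is exactly the waiting-time effect, so that any urgent subset of the 60 must fall short. That holds only with the control-arm variance. With the average variance the effect is 0.10/√0.1275 = 0.28 SD, and 60 × (0.25/0.28)² ≈ 48 urgent of 60 would match the waiting-time power. The two printed figures are compatible at equal cell sizes.

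Nor can it be said without qualification that a true 10-point gain would usually be missed. Without the gap, only the 20% share in the five-quarter wedge falls below one half. The lower figures come mainly from the gap, which affects the waiting-time power too, so they cannot be presented as independent of it. Finally, Table 3 lists patients seen within thresholds, not this urgent-only proportion, as primary.

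The defence does not rescue the figure in the described layout: even with all 100 expected referrals counted as urgent, power is 77%.

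**Conclusion.** The printed power does not follow from the stated inputs, because the cell sizes count all referrals and no urgent count is given. In the layout the article describes, it is not reached at any urgent share of the 60 or the 100: 16 to 32% at assumed shares of 20 to 50% of 60, and at most 55% or 77% if every referral were urgent. The implementation gap is the larger cause and the missing urgent count the smaller.

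The result rests on an ICC of 0.1 carried over from waiting time, the average binary variance, a constant effect, and a two-sided normal approximation. The 100 is a minimum average; specialties would need about 144 urgent referrals per quarter to bring the described layout to 90%. A test of two proportions that ignores clustering and calendar time gives 95% at a 20% share of 60 (28 × 12 = 336 per condition), but that is not the planned analysis.

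**What to change.** In the Sample size section, replace the statement of power above 90% for this outcome with power recomputed for the planned binomial mixed model. The calculation should use:

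- the expected number of urgent referrals per cluster-quarter, from the two years of historical clinic data collected for STAT Step 1, or a stated range of urgent shares such as 20 to 50% if the count cannot be fixed now;
- a stated ICC for this outcome;
- only the quarters that enter the analysis.

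Give the smallest change in the proportion detectable with 80 to 90% power. Describe the outcome as well powered only if that calculation supports it; otherwise present it as an estimate with a confidence interval.

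The cost is one re-run of the power calculation and one rewritten sentence. No cluster, period or patient is added. The downside is a less favourable stated figure.
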